### Allocation of participants

After signing the informed consent, the participant will receive an email with a link to the electronic baseline questionnaires. Once the questionnaires are completed, block randomisation (block size is 4) will be done by a computer-generated sequence in a 1:1 ratio on the individual patient and location level. Allocation in blocks of 4 is concealed and done using a central computer. Participants are either allocated to the motherfit programme (intervention) or the CAU (control group).

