### Interventions

#### Care-as-usual

In case participants with SUI are allocated to the CAU group, participating case managers give their normal advice and women make their own choices as to whether they want to participate in any kind of pregnancy-related course, visit to a physician or therapist.

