### Data collection and outcome measures

All data (electronic case report forms and questionnaires at baseline and follow-up) of the participants and case managers will be collected in a (web-based) digital central database. Demographic variables and personal characteristics will be registered by the Nederlandse Vereniging voor Obstetrie & Gynaecologie vragenlijst (NVOG-q) at baseline for MOTHERFIT1 and MOTHERFIT2.

MOTHERFIT1: data will be collected at baseline, 34 weeks of gestation, 6 weeks and 6 and 18 months post-partum.

MOTHERFIT2: data will be collected at baseline and 4, 9 and 18 months post-partum.

The case manager fills in a first survey after the inclusion of a participant. For MOTHERFIT1 these questions include, among others, expected delivery date and current medication use. Two weeks after delivery, case managers receive a second survey regarding delivery variables. For MOTHERFIT2 the case manager fills in identical surveys, except the question on expected delivery date.

Participants in the intervention group fill in a training diary and three questions regarding their general physical activity level, weekly. The PPTs will register attendance of the participant during the intervention period and send it by postal mail to the researcher.

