### Adherence to home training programme

Only participants in the intervention group register their performance of requested pelvic-floor-muscle exercises, including their general physical activity, weekly, at home in the training diary. The training diary is a data entry form and, if scanned, an Excel file will be computer generated.

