### Economic evaluation

#### General considerations

For both subgroups in MOTHERFIT1 and MOTHERFIT2, separate trial-based economic evaluations (EE) will be performed, but both EEs will have the same characteristics, except for the time horizon. The EE will take a societal and health care perspective, comparing motherfit group therapy with CAU. The time horizon for MOTHERFIT1 will be (about) 24 months starting from 12 weeks’ gestation (study inclusion) up to 18 months post-partum and for MOTHERFIT2 from approximately 6 weeks to 18 months post-partum. Cost-effectiveness ratios will be expressed as the societal cost per quality-adjusted life-year (QALY) (societal perspective), and the (health care) cost per woman, in whom UI is clinically relevant, reduced (primary outcome; health care perspective). Bootstrap analysis and cost-effectiveness acceptability curves will be constructed, showing for a range of threshold values the probability that motherfit group therapy is cost-effective. Sensitivity analyses and subgroup analyses (e.g. on age categories, adherent versus non-adherent women) will be performed to test for the robustness of the results.

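### An adherent versus non-adherent subgroup cannot test the robustness of the motherfit-versus-CAU economic evaluation, because adherence arises after randomisation and is recorded in one arm only

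*Protocol article*

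**What the plan says.** Under Economic evaluation, General considerations, the comparison is fixed: "The EE will take a societal and health care perspective, comparing motherfit group therapy with CAU". The ratios are cost per QALY and cost per woman with a clinically relevant reduction in incontinence. The same section then says that "subgroup analyses (e.g. on age categories, adherent versus non-adherent women) will be performed", and gives the purpose of these and the sensitivity analyses as "to test for the robustness of the results".

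Four other sections settle when and in whom adherence is seen:
- Allocation of participants: "Once the questionnaires are completed, block randomisation (block size is 4) will be done". Allocation therefore precedes any training.
- Adherence to home training programme: "Only participants in the intervention group register their performance of requested pelvic-floor-muscle exercises".
- Data collection and outcome measures: "Participants in the intervention group fill in a training diary and three questions regarding their general physical activity level, weekly". For the sessions, "The PPTs will register attendance of the participant during the intervention period".
- Care-as-usual: "participating case managers give their normal advice and women make their own choices". No programme is prescribed in that arm.

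The article gives no cut-off for adherence and names no method that would keep the randomised comparison within this subgroup.

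**The concern.** An incremental ratio against CAU within a subgroup is protected by randomisation only if the subgroup can be identified in both arms from information that allocation cannot influence. Age meets that condition and adherence does not. No CAU woman can be classed as adherent or non-adherent, so the like-for-like comparator for adherent motherfit women does not exist in the data.

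Women who keep training may differ from those who stop in motivation, severity or expected recovery. The Discussion itself treats adherence as strongly predictive of lasting results. That association may be partly causal and partly prognostic, and a split of the motherfit arm cannot separate the two. Costs are exposed as well: the Cost-analysis section counts group sessions, travel and time spent on the programme, all of which can vary with attendance.

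What is at stake is interpretation. Because adherence is listed beside age as a robustness check, a reader could take a favourable ratio in adherent women as confirmation of the main result.

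**Working it through.** **Step 1. Can the subgroup be formed in both arms?**

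| Variable | Known before allocation | Recorded in CAU | Subgroup keeps the randomised comparison |
|---|---|---|---|
| Age category | yes | yes | yes |
| Home-training adherence (diary) | no | no | no |
| Session attendance | no | no sessions in CAU | no |

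Two contrasts remain possible for adherence. One sets adherent (or non-adherent) motherfit women against all CAU women, which is not a randomised comparison. The other sets adherent against non-adherent women within the motherfit arm, which contains no CAU and so cannot test a motherfit-versus-CAU ratio.

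**Step 2. Reproduce the plan's own scale (Sample size calculation, MOTHERFIT1).** Inputs: expected 18-month means of 8 (CAU) and 5 (motherfit), SD 5, two-sided alpha 0.05, power 0.90.

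n per arm = 2 × (1.960 + 1.282)² × 5² / 3² = 58.4, so 59 (60 with the t distribution). The plan states 60, and 60 / 0.8 = 75. Both are reproduced, so a difference of 3 with SD 5 is the right yardstick for this trial.

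**Step 3. Apparent difference with no true effect.** Assumptions, none of them in the protocol: the better-adhering half of the motherfit arm is compared with all CAU women, and the trait behind adherence correlates r with a better 18-month score. The mean of the upper half of a standard normal distribution is 0.798, so

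apparent difference = 0.798 × r × 5.

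| r | Apparent advantage (points) | Share of the planned 3 |
|---|---|---|
| 0 | 0 | 0% |
| 0.1 | 0.40 | 13% |
| 0.2 | 0.80 | 27% |
| 0.3 | 1.20 | 40% |

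**Step 4. Sensitivity to the adherent share.** A simulation under the same null, with the adherent share varied from 30% to 70%, gives an advantage of 0.24 to 0.59 points at r = 0.1 and 0.74 to 1.74 at r = 0.3. The larger values belong to the smaller adherent group. Non-adherent women show a corresponding apparent harm. At r = 0 both differences vanish apart from simulation error.

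**Step 5. Effect on a nominal 5% test.** With 30 adherent women against 60 CAU women and no true effect, a two-sided test on the score rejects in about 6% of trials at r = 0.1 and 18% at r = 0.3.

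**The case against.** The protocol does not say that adherent women will be set against all CAU women. It gives neither comparator nor method for this item, and a condensed article may leave such detail to a fuller document. A within-arm description would fit the words. This is fair as far as it goes: the faulty ratio is inferred from the stated comparison, not written out. But the protocol does state the subgroup and its purpose, and a within-arm contrast cannot serve that purpose.

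The item is also small: one of two examples in a closing sentence on supporting analyses. That stands. The main analysis is by intention to treat, and neither it nor the sample size depends on this subgroup.

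A reader might infer more than the documents support:
- That the subgroup result would be nothing but selection. It would mix selection with any real effect of training, in unknown proportion.
- That adherent women will look cost-effective even if motherfit does nothing. The direction is not determined, because women who attend more may also incur more programme, travel and time costs.
- That the biased figure enters the budget impact analysis. That section models uptake and acceptability of the programme and does not say that estimates from this subgroup are inputs.
- That 13 to 40% applies to both trials. It uses MOTHERFIT1's 3-point difference; MOTHERFIT2 is planned on different means.

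**Conclusion.** The point holds as a limited but clear design fault in a supporting analysis. Adherence is a post-randomisation variable seen in one arm, so an adherence-specific ratio against CAU would be confounded by selection and is not a robustness check on the randomised comparison.

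The 0.4 to 1.2 points are an illustration. They rest on an assumed correlation of 0.1 to 0.3 and a median split, and apply to MOTHERFIT1 alone. They are also on the ICIQ-UI-SF score, whereas the economic outcomes are QALYs and the proportion of women with a clinically relevant reduction. No size can be given for the bias in costs or in the ratio itself from what the protocol reports.

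**What to change.** Remove adherent versus non-adherent women from the list of subgroup and robustness analyses, and restrict subgroups to variables known at baseline in both arms, such as age. Report adherence, with outcomes and costs by adherence level, descriptively within the motherfit arm and label it exploratory.

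A complier-average estimate with randomised arm as instrument is optional and supplementary only. It needs an adherence threshold set in advance. It also needs an explicit statement that it assumes allocation has no effect on outcomes or costs in women below the threshold. That is doubtful here, because such women may still have attended some sessions and received instruction and the app, all of which carry cost and possibly benefit.

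The required change is one line of wording and no new data. What is given up is an adherence-specific cost-effectiveness ratio, which the design cannot support as a randomised comparison. The optional estimate would cost one further model, would be less precise, and would rest on the assumption just described.

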### Cost-analysis

The cost-analysis will be performed from both a societal and health care perspective. Resource use will be measured in natural units and will be valued in monetary terms by multiplying these units by the costs per unit. If available, standardised, national cost prices (e.g. specified by the recently updated Dutch guideline for cost research in health care will be used [46]. Costs are distinguished into motherfit programme costs including the group sessions and home-based part and costs of the mApp (initial and replacement costs for ICT hardware and software), health care costs (e.g. use of incontinence materials, visits to the general practitioner, gynaecologist, midwifery costs, visits to the PPT, surgery, etc.), non-health care costs (e.g. travel costs and productivity losses) and patient and family costs (time spent on the programme, informal care costs). Data on (health care) resource utilisation associated with SUI will be prospectively recorded during the study by the participants. Other health care, non-health care and patient and family costs will be collected by means of a standardised cost questionnaire to be filled out by patients. Costs occurring 12 months after study inclusion will be discounted at 4% according to the Dutch guidelines for economic evaluations health care [47].

### Patient outcome analysis

The outcome for the cost-utility analysis (societal perspective) is defined in terms of QALYs from inclusion up to 18 months post-partum. The number of QALYs is derived from the adjustment of survival data with HRQL. HRQL will be measured with the EuroQol-5D (EQ-5D) instrument, which provides a descriptive health profile and a Dutch valuation set for obtaining utility scores from the EQ-5D [45]. The outcome for the cost-effectiveness analysis (health care perspective) is based on the proportion of women with clinically relevant reduction in UI at 18 months post-partum. Outcomes occurring 12 months following study inclusion will be discounted at 1.5% according to the Dutch guidelines for economic evaluations of health care [47].

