### Participants

Women will be included if they meet all of the following criteria: (1) aged ≥ 18 years, (2) UI (stress or mixed with predominant stress UI factor, according to Haylen et al. [6], (3) a score of > 3 on the International Consultation on Incontinence Modular Questionnaire-Urinary Incontinence-Short Form (ICIQ-UI-SF) questionnaire [27], (4) are motivated for participation in the motherfit programme, (5) are competent to speak and understand the Dutch language and to read and fill in forms independently and (6) have a mobile app (mApp) on a tablet (Apple or Android) available.

Exclusion criteria are: (1) UI prior to first pregnancy, still existing during pregnancy, (2) high-risk pregnancy, resulting in a contra-indication for performing intensive pelvic-floor-muscle (PFM) exercises (e.g. placenta praevia, vaginal blood loss, preterm uterine contractions), (3) suffering from significant exercise limitations or co-morbidities (physical or psychological) that would restrain a woman from participation in motherfit group therapy, (4) a history of chronic neurological disorders or diseases related to UI (e.g. multiple sclerosis, cerebrovascular accident, diabetes mellitus (during ≥ 1 year with glycated hemoglobin (HbA1c) > 10 mmol/l)), (5) urinary tract infection (urine-sediment, urine culture), (6) a history of anti-incontinence or urogynaecological surgery, (7) women who are expected to be lost to follow-up (e.g. because of a planned change of residency), (8) have had recent pelvic physiotherapy (< 6 months) and (9) refusal to use a mApp.

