### Primary outcome measure

Tables 1 and 2 show the schedule of assessments for MOTHERFIT1 and MOTHERFIT2. The primary outcome measure is self-reported UI based on the severity sum score of the ICIQ-UI-SF. The ICIQ-UI-SF is a brief (four questions) and robust measure for evaluating the frequency of symptoms and impact of UI [34]. The total score ranges from 0 (not affected) to 21 (severely affected). The ICIQ-UI-SF is divided into the following four severity categories: slight (1–5), moderate (6–12), severe (13–18) and very severe (19–21) [35]. The questionnaire is translated in Dutch [36]. Therapy success is defined as absence of UI or change from baseline of at least 3 points on the ICIQ-UI-SF at 18 months post-partum [37].

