## Statistical methods

### Sample size calculation

Assuming that the average score of the primary outcome measure (ICIQ-UI-SF; range 0–21) of MOTHERFIT1 will lie at 8 and for MOTHERFIT2 at 9 (which is also the expected mean ICIQ-UI-SF score at 18 months post-partum in the CAU group; in contrast, the expected mean ICIQ-UI-SF score at 18 months post-partum in the experimental group is 5 (for MOTHERFIT1 and MOTHERFIT2) together with a relatively high standard deviation of 5 at baseline (because of the non-normality of the measure), participants will – with 97.5% probability – vary at baseline within the ranges of 0 to 19. The minimum acceptable score of participants to be treated is set at 3, so the range lies approximately between 3 and 19. From earlier studies [44], it became clear that the success of the PFMT exercises will be considerable and will be clinically relevant if the gain is higher than half the standard deviation of the baseline, presumably 3 with a somewhat smaller standard deviation of 3, because of the homogenising effects in the experimental arm. In contrast to MOTHERFIT1 (women remain stable), in MOTHERFIT2 it is assumed that the condition of CAU participants at 18 months will worsen with an average ICIQ-UI-SF score going from 9 in the baseline to 10 (SD 5).

Assuming two-sided testing, a power of 90% (beta = 0.10) and a significance level of 0.95 (alpha = 0.05) in each arm of the trial in MOTHERFIT1, minimally 60, and in MOTHERFIT2, minimally 35 participants will have to be included without taking into account that participants may drop out of the study during the 18 months of observations. Using a 20% dropout, in MOTHERFIT1 each arm will need 75 participants, 150 in total, and in MOTHERFIT2 each arm will need 45 participants, 90 in total.

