### Analysis of main hypotheses

In both studies, the main hypothesis concerns differential changes in ICIQ-UI-SF within time between two randomised groups of participants. (Repeated measurements) analysis of covariance (ANCOVA) will be performed with baseline measurements (T0) as covariate. Transformations of original scores will be attempted if the ICIQ-UI-SF shows a non-normal distribution at T0. Randomisation groups (motherfit group therapy versus CAU) are regarded as a between factor. Next, the within-participants linear trend in time of the outcome will be calculated with the weights from the first orthogonal polynomial contrast and this is used as a dependent variable in a multiple (dummy-)regression analysis. It concerns repeated measurements from T0 to T4 (MOTHERFIT1) and T0 to T3 (MOTHERFIT2). Next to the baseline covariate measurement and the randomisation groups’ dummy variable, other possible confounding variables will be used in this multiple linear regression analysis of the linear trend in time of the ICIQ-UI-SF.

The following potential confounding variables are considered to be used in the multiple linear regression analysis: Body Mass Index (BMI) before pregnancy (> 25), parity, maternal age (> 35 years) and the ability to perform a PFM contraction at baseline.

Forward selection and backward elimination techniques will be used to determine the best fit of the data to a final regression model. Testing of interactive relationships between statistically significant effects of predictors in the final model will be done, especially if it concerns the experimental between-randomisation groups’ factor. Listwise deletion of missing cases will be used in all linear regression modelling. This may be in case of loss-to-follow-up because of a succeeding pregnancy during the follow-up period of 18 months. For the final best-fitting regression model, a residual analysis will be done on the standardised Studentised z-scores and a screening will be performed on outliers to ensure the legitimacy and validity of the use of parametric statistics in analysis by testing the normality of distribution of the linear trend in ICIQ-UI-SF.

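### No baseline adjustment is stated for the responder difference behind the health-care cost ratio; adjusting it for T0 ICIQ-UI-SF would be a free but modest gain in precision

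*Protocol article*

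**What the plan says.** Under Patient outcome analysis, the outcome for the health-care cost-effectiveness analysis "is based on the proportion of women with clinically relevant reduction in UI at 18 months post-partum". General considerations expresses the ratio as "the (health care) cost per woman, in whom UI is clinically relevant, reduced" and labels this the primary outcome. On uncertainty it says "Bootstrap analysis and cost-effectiveness acceptability curves will be constructed". No covariate is named in either place.

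Primary outcome measure gives the rule for response: "Therapy success is defined as absence of UI or change from baseline of at least 3 points on the ICIQ-UI-SF".

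Under Analysis of main hypotheses, the ICIQ-UI-SF comparison is an analysis of covariance that "will be performed with baseline measurements (T0) as covariate". The paragraph that follows extends this handling to secondary outcomes, with the IIQ-7, the GPE and the EQ-5D-5L as examples. The responder proportion is not among them.

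**The concern.** The same questionnaire supplies both the clinical effect and the effect in the health-care ratio, but T0 adjustment is stated only for the first. Basing response on change from T0 does not remove the influence of T0. Entry requires "a score of > 3 on the International Consultation on Incontinence Modular Questionnaire" and the scale stops at 0, so a woman who enters at 4 must reach 0 or 1 to count as a responder. A woman who enters at 15 need only reach 12, and regression to the mean helps her.

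If T0 predicts response, an unadjusted responder difference carries variance that a covariate recorded before randomisation could remove. That difference is the denominator of the cost per responder, and trial effectiveness data also feed the long-term model.

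**Working it through.** **Inputs.** From Sample size calculation:
- T0 means: "of MOTHERFIT1 will lie at 8 and for MOTHERFIT2 at 9"; T0 SD 5.
- Motherfit 18-month mean 5, with an SD of 3.
- CAU SD 5. The CAU mean is 8 in MOTHERFIT1. In MOTHERFIT2 the section gives both 9 and 10; the simulation below uses 10.
- 60 and 35 women per arm before dropout.

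The correlation between T0 and the 18-month score is not given. It is assumed to be 0.3, 0.5 or 0.7.

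**The plan's own figure.** The article states no expected responder proportion or cost per responder. The sample size can be checked as n = 2(1.960 + 1.282)² × SD²/δ² per arm.
- MOTHERFIT1: 2 × 10.51 × 25/9 = 58.4, so 59 (60 by t-test; stated 60).
- MOTHERFIT2 with δ = 9 − 5 = 4: 2 × 10.51 × 25/16 = 32.8, so 33 (34 by t-test; stated 35).
- Dropout: 60/0.8 = 75 and 35/0.8 = 43.75, so 44 (stated 75 and 45).

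These agree to within 2 women per arm.

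**Response reduces to a fall of 3 or more.** T0 is at least 4, so absence of UI always means a fall of at least 4. The first half of the success rule therefore adds nobody.

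**Dependence on T0, taking SD 3 as the SD of the 18-month score.** The expected fall per extra T0 point is 1 − ρ × SD₁₈/SD₀.
- Motherfit: 1 − 0.6ρ, which is 0.82, 0.70 and 0.58 at ρ = 0.3, 0.5 and 0.7.
- CAU: 1 − ρ, which is 0.7, 0.5 and 0.3.

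Simulated MOTHERFIT1 responder rates at ρ = 0.5:

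| T0 | CAU | Motherfit |
|---|---|---|
| 4–5 | 17% | 24% |
| 6–12 | 32% | 64% |
| 13–18 | 58% | 97% |

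**Precision.** The unadjusted risk difference was compared with one adjusted linearly for T0 with an arm-by-T0 term, over 4,000 simulated trials per setting. T0 was rounded and cut to 4–21.

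| Trial (per arm) | ρ | Mean difference, unadjusted / adjusted | SE, unadjusted / adjusted | Variance cut |
|---|---|---|---|---|
| MOTHERFIT1 (60) | 0.3 | 0.255 / 0.256 | 0.087 / 0.077 | 22% |
| | 0.5 | 0.296 / 0.297 | 0.087 / 0.079 | 17% |
| | 0.7 | 0.372 / 0.373 | 0.084 / 0.079 | 11% |
| MOTHERFIT2 (35) | 0.3 | 0.393 / 0.394 | 0.111 / 0.098 | 22% |
| | 0.5 | 0.450 / 0.452 | 0.108 / 0.098 | 16% |
| | 0.7 | 0.549 / 0.551 | 0.100 / 0.093 | 12% |

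The mean difference does not move, so adjustment corrects no bias. The SE falls by about 6–12%.

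**Sensitivity.**
- A repeat of the simulation on this reading gave a variance cut of about 7–22%.
- Cutting a normal distribution at 4 raises the simulated T0 mean to about 9.6 and 10.2 and shrinks its SD to about 3.8 and 3.9. With T0 centred on the stated means instead, the cut is about 3–16%.
- If the SD of 3 is that of a gain independent of T0, the cut is 0 to 2.5% in MOTHERFIT1 and −1% to +2% in MOTHERFIT2.

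**Chance imbalance is the same component.** In MOTHERFIT1 the SD of the T0 mean difference is about 0.68 points. A one-SD imbalance shifts the responder difference by 0.041, 0.037 or 0.029 at ρ = 0.3, 0.5 or 0.7. As a share of the unadjusted variance:
- 0.041²/0.0872² = 22%
- 0.037²/0.0869² = 18%
- 0.029²/0.0839² = 12%

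These match the variance cuts of 22%, 17% and 11%.

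**The case against.** The strongest case is that the sentence names an outcome and not an estimator. A reader might infer that the article commits to raw proportions. It does not use that word or any equivalent, and a standardised, T0-adjusted proportion would fit the sentence as written. The article also condenses a fuller protocol, which may settle the point. This stands as a limit on the wording: the unadjusted reading is the natural one but not an explicit commitment. It does not remove the suggestion. The economic section is fairly specific (perspectives, horizons, discount rates, bootstrap), and the adjustment stated elsewhere is not carried over to this outcome.

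A reader might also infer that the ratio would be biased, or that chance T0 imbalance is a second harm on top of lost precision. Neither is supported. Randomisation keeps the unadjusted difference unbiased, and the imbalance is already inside its standard error and any bootstrap interval. Nor do the two sections contradict each other: they concern different analyses.

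The size rests on one reading of an ambiguous sentence. In Sample size calculation, the SD of 3 can be read grammatically as the SD of the gain, and on that reading the benefit can vanish. This objection stands. The reference there to homogenising effects in the experimental arm fits the 18-month score better, but does not settle it.

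Finally, the article gives no cost figures, so no effect on the acceptability curve can be calculated.

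**Conclusion.** The point holds as an efficiency improvement and not as an error. No T0 adjustment is stated for the responder difference in the health-care ratio, although the clinical analysis of the same instrument has one. Adjustment would reduce the variance of that difference by roughly 3–22% if the motherfit SD of 3 describes the 18-month score, with an assumed correlation of 0.3–0.7 and depending on the T0 distribution. It would reduce it by about nothing if the SD of 3 describes a gain independent of T0. The unadjusted estimate remains valid, and the expected gain is modest.

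**What to change.** Add one sentence under Patient outcome analysis: the effect in the health-care ratio is the T0-adjusted difference in the proportion with a clinically relevant reduction. Within each bootstrap sample, regress response on arm and T0 ICIQ-UI-SF and standardise over all randomised women to obtain the difference. Use it in the ratio and the acceptability curve, and report the raw proportions descriptively.

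This also settles the choice between an adjusted and an unadjusted ratio before the results are seen. The cost is one sentence and a few lines of analysis code. T0 is completed before randomisation, so no new data are needed.
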